## Abstract

**Background:**

Alzheimer’s disease (AD) is the most common type of dementia in the elderly. It is estimated that the global prevalence of dementia will rise from 24.3 million in 2005 to 81.1 million in 2040. AD has a devastating impact on sufferers, caregivers, their communities and the healthcare system in general. “Di-tan decoction” (DTD) is a traditional Chinese medicine (TCM) formula frequently used to treat symptoms that are now defined as AD in clinical treatment. However, the existing evidence for recommending DTD in clinical practice derives from studies that were methodologically flawed. In this study, we aim to determine the efficacy and safety of DTD in AD patients based on a rigidly randomized controlled trial. It will provide critical information on sample size and treatment regimen for conducting a full-scale clinical trial of DTD later.

**Methods/Design:**

This study will be a double-blind, randomized, placebo-controlled, add-on trial. After a 2-week run-in period, eligible patients with mild to moderate AD will be recruited and given either DTD or placebo twice daily for 24 weeks with follow-up 6 weeks after the last treatment. An increase of four points or greater on the scores of Alzheimer’s Disease Assessment Scale-cognitive subscale (ADAD-cog) will be considered as a positive primary outcome. Total scores of the ADAD-cog, the Chinese version of Mini-Mental State Examination (C-MMSE), and the Chinese version of the Disability Assessment for Dementia (C-DAD) score will be used as secondary outcomes. Adverse events will also be reported.

**Discussion:**

This randomized trial will be the first rigorous empirical study on the efficacy of DTD for treating cognitive symptoms in AD patients. Its success will justify and warrant a large-scale clinical trial to further consolidate the evidence for DTD’s efficacy in treating AD.

**Trial registration:**

Chinese Clinical Trial Registry (ChiCTR-TRC-12004548, Date of registration: 22 November 2012)

**Electronic supplementary material:**

The online version of this article (doi:10.1186/s13063-015-0716-z) contains supplementary material, which is available to authorized users.

## Background

Alzheimer’s disease (AD) is an irreversible, progressive neurodegenerative disorder characterized by loss of cognitive functions, behavioral disturbances and daily living difficulties [1]. It is the most common type of dementia in the elderly [2]. Progressive atrophy is seen in all parts of the brain, especially in the hippocampus region, due to nerve cell death and tissue loss [3]. It is estimated that the number of people suffering from dementia over the world will rise from 24.3 million in 2005 to 81.1 million in 2040 [4]. It is expected that a new case of AD will be diagnosed every 33 seconds in America by 2050 [5].

AD has a devastating impact not only on sufferers, but also on caregivers, their communities and the health care system in general [6]. While much research is being done on many aspects of AD, including its basic biology, no drug has been found to alter the course of the disease [7]. Current pharmacological treatment for AD such as cholinesterase inhibitors (ChEIs) and memantine are symptomatic and may commonly associated with some side effects, such as nausea, vomiting, dizziness and anorexia [8]. Given that the efficacy is mild but with some side effects, patients often seek alternative treatments [9].

In traditional Chinese medicine (TCM), AD is described in terms of TCM principles; it could be caused by (1) a deficiency of vital energy of the kidney, heart and spleen or (2) the stagnation of blood and/or phlegm [10]. The guidelines that classified dementia into different subtypes according to the TCM theory was published in 1990, and symptoms of “phlegm turbidity obstructing the orifices” (PTOO) is considered to be one of the major contributing factors to AD [11]. Thus, the primary TCM strategy for treating AD is to “resolve phlegm in order to open the orifices” [12]. The classic Chinese medicine formula “Di-tan decoction” (DTD) was developed by a famous TCM doctor, Dong Su, in 1449 with the specific function of “resolving phlegm to open the orifices” [13]. It has been and still is frequently used to treat symptoms that are now defined as AD in clinical treatment with TCM [14,15]. In recent years, modern studies have attempted to verify the clinical effects of DTD in biochemical terms. Laboratory studies have shown that the memory impairment of AD model mice was significantly reduced by DTD [16,17]. In the brain tissue in mice treated with DTD, acetylcholine (Ach) and acetylcholine transferase (ChAT) were significantly increased, while acetylcholine esterase (AchE) was decreased [18]. The results of another study indicate that DTD may inhibit the decline of the dopamine content in brain tissue of model mice as well [19].

In our previous systematic review, there was no clinical trial using DTD as the main intervention for treating AD. For the AD clinical trials that had involved DTD as an adjunct intervention, we found that most of them support the efficacy of DTD in treating AD. However, the evidence for recommending DTD in clinical practice derives from studies that were methodologically flawed. None of them was a randomized controlled trial. They not only lacked randomization, blinding, and the use of control groups, but also failed to define inclusion and exclusion criteria and the quality of the intervention medicine [20]. Because of the methodological problems in previous studies, evidence to suggest that DTD is effective in treating AD is not strong. There is a lack of conclusive evidence to recommend a clinical trial.

As there is no basic information of DTD to conduct a comprehensive AD clinical trial, a rigorous pilot study, which focuses on the efficacy and safety of DTD for treating AD, will be needed before conducting a full-scale clinical trial. In this study, we will evaluate the efficacy and safety of DTD in patients with AD in a randomized controlled trial. This study will be a randomized, double-blinded, placebo-controlled study, with restrictive inclusion and exclusion criteria and a clearly defined quality control intervention medicine. We hope the results from this study will provide critical information on sample size and treatment regimen for conducting a full-scale clinical trial later.

## Methods/Design

### Study design

This study will be a double-blinded, randomized, placebo-controlled, add-on trial. Patients with mild to moderate AD will be randomly assigned to receive 24 weeks of either active herbal treatment or placebo (in a 1:1 ratio); they will be followed for a further 6 weeks’ observation period without treatment. This clinical study will be carried out at the Hong Kong Baptist University Chinese Medicine Specialty Centre. It has been approved by the Ethics Committee of the Hong Kong Baptist University’s Institutional Review Board (code: HASC/11-12/24) and registered with the Chinese Clinical Trial Registry (ChiCTR-TRC-12004548). If there is any amendment to the protocol, approval must be again sought from the Ethics Committee. Written informed consent will be obtained from every patient before participation in any study-related activity. The protocol design is based on the guidelines of Consolidated Standards of Reporting Trials (CONSORT) and Standard Protocol Items: Recommendations for Interventional Trials (SPIRIT) [see Additional file 1], and study results will be reported according to these guidelines as well.

### Participants

Inclusion criteria are as follows: Adults who (1) have been clinically diagnosed with AD based on the criteria of National Institute of Neurological and Communicative Disorders and Stroke and Alzheimer’s Disease and Related Disorders Association (NINCDS/ADARA) [21], and (2) present symptoms classified as PTOO [see Additional file 2] as defined by the Guidance for Clinical Research of New Chinese Herbal Medicine [22] during a screening visit, will be eligible. The diagnostic criteria of PTOO include dementia, heavy-headedness and spitting phlegm. Additional inclusion criteria are as follows: (1) mild to moderate dementia with ≥2 on Clinical Dementia Rating Scale (CDR) [23]; (2) receiving a stable dose of anti-dementia medication (that is, Donepezil, Rivastigmine and Memantine) for at least 4 weeks before the start of treatment; and (3) normal liver and renal function.

Exclusion criteria are as follows: Patients who also have any other type of dementia (that is, vascular dementia), and/or other neurodegenerative disorder (that is, Parkinson’s disease), depression (defined by a score of ≥8 on the 15-item Chinese version of the Geriatric Depression Scale [24]), or who are unwilling to cooperate with treatment procedures will be excluded. For those who have participated in other trials within 30 days of the start of this trial as well as women who are pregnant or breastfeeding will also be excluded.

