## Discussion

AD, as a progressive neurodegenerative disorder, has devastating impacts not only on patients but also on family members, friends, and caregivers. A cure would bring immeasurable relief and hope to countless thousands. Unfortunately, western pharmacological research has been unsuccessful in finding effective treatment without serious side effects [8]. In this case, Chinese medicine may have something to offer. Chinese medicine has been used to treat neurological diseases for thousands years with efficacy, safety, and relatively few side effects - albeit without rigorous and objective testing [33].

This randomized trial will be the first rigorous testing of DTD for the treatment of AD patients. Success in this clinical trial will provide evidence acceptable to the scientific community of the potential of DTD to become an effective medicine for AD. The success of this study would represent justification and impetus for a large-scale clinical trial to further consolidate the evidence for the use of DTD in the treatment of AD.

It is noted that the sample size calculation does not apply to this study. Normally, 10 to 20 patients in each group would be sufficient to implement the method of a pilot study [34]. Since there is no previous data indicating the sample size needed to unequivocally determine the effect of DTD by the ADAS-cog, the evidence will still be weak even if we have a positive result. Nevertheless, the one aspect of this study that could undermine its value is sample size. There is no information on what sample size is needed to give statistically significant results. On the other hand, this study could find out what specific symptoms, like mood or cognitive, that DTD may improve. This information should be an important evidence for a much precise clinical trial with larger sample size in the future.

In conclusion, the results of this study are expected to provide evidence for the efficacy and safety of the Chinese herbal formula, DTD, for treatment of AD patients who also meet the diagnostic criteria of “phlegm obstructing the orifices” syndrome according to TCM diagnostics. It may also provide a new direction for the clinical research on AD and TCM.

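### The CDR criterion in the Protocol article contradicts its own wording and the stated mild-to-moderate population

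*Protocol article*

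**What the plan says.** The Abstract (Methods/Design) says that "eligible patients with mild to moderate AD will be recruited", and the Study design section says "Patients with mild to moderate AD will be randomly assigned".

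The Participants section turns this into a screening rule: "mild to moderate dementia with ≥2 on Clinical Dementia Rating Scale (CDR". This is the only CDR rule in the article. It does not say whether the global score or the sum of boxes is meant, and it does not print the scale's anchors.

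The exclusions in the same section begin with "Patients who also have any other type of dementia (that is, vascular dementia), and/or other neurodegenerative disorder" and go on to depression, unwillingness to cooperate, recent participation in another trial, and pregnancy or breastfeeding. None of them refers to severity.

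The Background presents the trial as one "with restrictive inclusion and exclusion criteria", having criticised earlier studies for not defining theirs.

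**The concern.** A range with two ends cannot be defined by a lower limit alone. If higher CDR means worse dementia, a threshold of 2 or more appears to remove the mild end and to leave the severe end open. The words in the same criterion say something else.

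Three things are at stake.

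- **Consistent screening.** Two screeners could decide differently on the same patient, one following the words and the other the number, and each could cite the protocol.
- **Use of the pilot.** The Background says the results will inform the sample size and regimen of a full-scale trial. Responder proportions and score variability from an unclear severity mix do not carry over safely to a mild-to-moderate population.
- **Interpretation.** The Recruitment procedures section plans 20 per arm, and allocation is by simple randomization. Nothing in the design protects against a chance imbalance in severity, so readers need to know what severity was enrolled in each arm.

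**Working it through.** No sample-size, power or error-rate formula applies. The check compares the set of patients the rule admits with the set the article says it wants.

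**Inputs from the article**

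- Intended population: mild to moderate (Abstract; Study design; first half of the criterion in Participants).
- Numeric rule: CDR of 2 or more, no upper limit (second half of the same criterion).
- Other criteria that could cap severity: none. There is no upper CDR limit, no MMSE range and no exclusion of severe dementia.
- Enrolment: 36 participants (Trial status), against at least 40 planned (Recruitment procedures).

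**Assumption not in the article**

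The global CDR is ordinal, with higher scores worse: 0 none, 0.5 questionable, 1 mild, 2 moderate, 3 severe. On this scale the intended set is {1, 2}.

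**Comparison**

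| Reading of the criterion | Admitted | Mild (1) | Moderate (2) | Severe (3) |
|---|---|---|---|---|
| Intended population | {1, 2} | in | in | out |
| Global CDR, number alone | {2, 3} | out | in | in |
| Global CDR, words and number both required | {1, 2} ∩ {2, 3} = {2} | out | in | out |

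On the global score the number and the stated population share only CDR 2. Whether the words are applied as well decides what happens to severe patients, but it does not bring mild patients back.

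**The other score type**

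If a sum-of-boxes score was meant, a threshold of 2 would not cut off the mild end. The number would still set no ceiling, so severity would be limited only by the words, which have no numeric definition. The lower end is then acceptable and the upper end is undefined.

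**Reach**

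40 − 36 = 4 participants remained to the planned minimum at manuscript submission. A wording change alone would therefore govern few further enrolments. The records of those already in matter more.

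**The case against.** The strongest reply is that the criterion has two parts and both must be met. A severely demented patient fails the words even when passing the number, and the Abstract and Study design also restrict the trial to mild-to-moderate disease. This stands. A reader might infer that the rule as written enrols moderate-to-severe patients; the article does not support that, because with both parts required the result is moderate only. The reply does not rescue the criterion, since mild patients are still shut out on the global score.

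A second reply is that the sign is simply reversed. On the assumed anchors, a rule of 2 or less admits {0, 0.5, 1, 2}, and together with the words it gives {1, 2}, the stated population. That is plausible, but nothing in the article settles it, and the published rule is the one a screener or reader would apply.

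A third reply is that the anchors and score type come from outside the document. That is correct, and the loss of the mild end depends on them. The one-sided form of the threshold does not.

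A fourth is that a journal article condenses the full protocol. Condensation explains missing detail. It does not explain a printed threshold that conflicts with the words next to it.

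Finally, this is a pilot, and the Discussion says "It is noted that the sample size calculation does not apply to this study". No sample-size figure depends on the CDR rule, and none is claimed to.

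**Conclusion.** The criterion is wrong as written. It contradicts itself and the mild-to-moderate population in the Abstract and Study design. Assuming the global CDR, one of the two intended severity bands (mild) is excluded under either reading. The severe band is admitted if the number is applied alone and excluded if the words are applied too. Assuming sum of boxes, the mild end is kept and the number gives no upper limit.

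Two further inferences are tempting and should not be drawn.

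- That the trial departs from its title, objective and conclusion. The title is not in the text available. The aims in the Abstract and Background and the conclusion in the Discussion refer to patients with AD, without a severity range.
- That most of the 36 participants breach the criterion. No baseline CDR data are given. What can be said is that, on the global score, any participant with CDR 1 fails the numeric rule.

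**What to change.** 1. Reconcile the Abstract, Study design and Participants sections. State which CDR score is used and give both bounds of the range that matches the intended population. If a threshold of 2 or more was intended, change the population wording instead. The choice is the sponsor's.
2. Obtain ethics approval. The Study design section requires approval, not just notification, for any amendment.
3. Check the screening CDR of the 36 participants already enrolled and of any since, and report any outside the reconciled range.
4. Tabulate baseline CDR by arm.
5. In the conclusions and in planning the full-scale trial, describe the population by the severity actually enrolled.

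The cost is a short amendment with ethics review, a check of existing screening records and one baseline table. No new data collection should be needed if screening CDR was recorded, as the criterion implies.

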### Study medication

The herbal medicine under study is DTD (Table 1). It is composed of Arisaema Cum Bile (DanNanXing in Chinese), Pinelliae Rhizoma (FaBanXia in Chinese), Aurantii Immaturus Fructus (ZhiShi in Chinese), Poria (FuLing in Chinese), Citri Reticulatae Pericarpium (ChenPi in Chinese), Acori Tatarinowii Rhizoma (ShiChangPu in Chinese), Ginseng Radix (RenShen in Chinese), Bambusae in Taeniam Caulis (ZhuRu in Chinese), Glycyrrhizae Radix (GanCao in Chinese), Zingiberis Recens Rhizoma (ShengJiang in Chinese) and dextin [13]. The test report of the DTD quality control is attached in the Additional file 3. The placebo is made of caramel (2%), gardenia yellow pigment (0.05%), sunset yellow (0.02%), tartrazine (0.02%), dextrin (95%) and broadleaf holly leaf (2.91%) [25]. The granules were produced in a single batch (DTD batch no.: A12074 Placebo batch no.: A120817) strictly in compliance with standards of Good Manufactory Practice (GMP) and Chinese Pharmacopoeia 2010 to ensure the stability and homogeneity of the composition as produced by PuraPharm Pharmaceuticals Company Limited. The chemical compositions of the final products were analyzed for contamination with heavy metals, toxic elements, microbe and pesticide residues; both final products were analyzed for stability and adherence to quality standards. The active treatment granules and the placebo granules have identical appearance and smell, and both have been packed in sealed opaque aluminum sachets and put in zip lock bags (10 sachets each). Only the treatment code is printed on the package to ensure successful blinding of patients [26]. One sachet contains 13.5 g, a dosage equivalent to 67.5 g herbs. All herbal and placebo granules will be distributed by [name] with both written and verbal instructions for each participant. Patients will be instructed to take the granules orally by dissolving a sachet of granules in 150 ml hot water, stirring well, then drinking the solution, two times per day, at least two hours apart from taking any routine Western medication. Patients will be allowed to discontinue the study granules temporarily if any adverse events occur. Patients will be instructed to report such events to a special e-mail account or by a direct telephone line. Additional treatments for a newly occurring illness, for example, flu or diarrhea, or adverse event during the study will be allowed but must be reported to the assessor.

**Table 1 Tab1:** **“Di-tan decoction” (DTD) composition**

**Chinese name**	**Latin name**	**Percentage**
Dan Nan Xing	Arisaema Cum Bile	11.42
Ban Xia	Pinelliae Rhizoma	11.42
Zhi Shi	Aurantii Immaturus Fructus	9.13
Fu Ling	Poria	9.13
Chen Pi	Citri Reticulatae Pericarpium	6.84
Shi Chang Pu	Acori Tatarinowii Rhizoma	4.55
Ren Shen	Ginseng Radix	4.55
Zhu Ru	Bambusae in Taeniam Caulis	3.19
Gan Cao	Glycyrrhizae Radix	2.29
Sheng Jiang	Zingiberis Recens Rhizoma	18.10
Dextrin	*-*	19.36

### Recruitment procedures

Three methods will be used to recruit participants with AD. The first source of candidates will be referral from two public Western medicine hospitals in Hong Kong (Prince of Wales Hospital and Queen Elizabeth Hospital) from our co-investigator (Co-I), [name], and our research teammate, [name]. The second source will be referral from the Chinese medicine clinic of Hong Kong Baptist University. A third source of candidates will be those who respond to advertisements published in local newspapers and newsletters of local AD societies.

Figure 1 shows the schedule of enrollment. We plan to recruit at least 40 patients, which will allow 20 for the DTD group and 20 for the placebo group in this study. All patients diagnosed with AD will be referred to a Chinese medicine doctor who is the Principle Investigator of the study ([name]), or to a Research Assistant ([name]), for further assessment and recruitment. The aim, procedures, nature of study and possible side effects of DTD will be explained by the PI or RA; then, each subject will be asked to sign a written consent [see Additional file 4] to take part in the study. Patients will be informed that they are free to withdraw at any time during the study.

**Figure 1 Fig1:**
[figure not shown]
Schedule of enrollment.

All patients will undergo a 2-week run-in period, in which they have to keep their Western medicine and supplement dosages fixed. Their blood will be tested to check liver function (alanine transaminase (ALT)/serum glutamic pyruvic transaminase (SGPT), aspartate transaminase (AST)/ serum glutamic oxaloacetic transaminase (SGOT), alkaline phosphatase, gamma glutamyltransferase, total bilirubin, total protein, albumin) and renal function (urea, creatinine, sodium, potassium, chloride, bicarbonate) in a lab test center designated for the project.

### Randomization and masking

The randomization sequence will be generated by SPSS 19.0 package (SPSS, Chicago, IL). The sequence will be password-protected and kept in a computer by [name]. Group allocation will be simple randomization in a ratio of 1:1 to either active treatment group or placebo group. The number sequences will be kept in sealed opaque envelopes and distributed to assessors. Patients, investigators and all sponsoring parties will be masked to treatment allocation until the end of the study. When there is a serious adverse event, the event will be discussed between the principal investigator Chinese medicine expert [name], and the co-investigator neurology specialist [name] to consider unblinding.

